### Strategies to improve adherence to interventions {11c}

CAFÉ navigators make up to 6 call attempts to reach a participant for each assessment visit, then send an “unable to reach” letter with our contact information and encouragement for them to reach out if they are still interested in participating.

### Relevant concomitant care permitted or prohibited during the trial {11d}

There are no restrictions regarding concomitant care during the trial. No alteration of usual care pathways is required for implementation of activities for any of the three trial arms (enhanced usual care; brief financial navigation; extended financial navigation).

### Provisions for post-trial care {30}

All study participants will continue to receive cancer care as determined through clinical shared decision making with their clinical care team.

### Outcomes {12}

Primary and secondary outcomes for the CAFÉ study are shown in Table 1. Primary outcomes include participant-reported financial distress and cancer-related quality of life at 12 months. Secondary outcomes include material, behavioral, and psychological financial hardship; global quality of life; patient-centered communication, and delayed or foregone care as measured by health service use at 12 months.

**Table 1 Tab1:** CAFÉ study endpoints

Objectives	Endpoints assessed at 12 months	Justification for endpoints
**Primary**		
1. To compare self-reported financial hardship between patients receiving the CAFÉ intervention versus a comparison group at 12-month follow-up.	Financial distress [InCharge Financial Distress/Financial Well-Being Scale] [41]	Financial hardship is an established social determinant of health.
1a: To compare self-reported health-related quality of life between patients receiving the CAFÉ intervention versus a comparison group at 12-month follow-up.	Health-related quality of life [cancer-specific: FACT-G7] [42]	Cancer-related financial hardship is directly associated with multiple adverse health outcomes (e.g., quality of life; pain, symptom burden, mortality).
**Secondary**		
2. Compare health service use between patients receiving the CAFÉ intervention versus a comparison group at 12-month follow-up.	Survey: Material, behavioral, and psychological financial hardship Medical Expenditure Panel Survey (MEPS) items [43] Global quality of life PROMIS Global health [44–47] Patient-centered communication: Patient Assessment of cancer Communication Experiences (PACE) [48] (EHR) Delayed or foregone care assessed by treatment initiation^a^ and time to treatment initiation^a^ Use of KP medical financial assistance services^a^; total out-of-pocket expenditure; account delinquency	The CAFÉ intervention could facilitate early identification of patient affordability concerns and care plan adjustments; improve access to financial planning resources or payment plans; and by connection to referrals and resources for acute financial distress.
3. Assess patient-level factors influencing variability in dose of the CAFÉ intervention.	Intervention dose received (Arm 2 vs Arm 3)	Estimation of ideal dose will be important for future implementation of the intervention.
**Exploratory/covariates**		
Exploratory	Difficulty paying bills, ongoing financial stress, medication reduction due to cost, food insecurity [49, 50]; difficulty living on current income [51]; decisional regret; decision satisfaction	The CAFÉ intervention may directly impact these endpoints but analyses are exploratory.
Covariates	Socioeconomic variables; clinical variables; existing financial burden; insurance characteristics (health insurance type; maximum out-of-pocket limit; deductible limit; co-Insurance or co-payment)	

^a^Health service use outcomes measured via EHR will be assessed at both 3 months and 12 months

### Participant timeline {13}

An individual’s participation duration is 12 months. A participant is considered to have completed the study if they have completed the baseline assessment, at least 1 intervention cycle (Arms 2 and 3 only; defined as one financial navigation visit plus associated follow-up contacts to resolve concerns identified in the visit), and the 12-month follow-up assessments (Table 2).

**Table 2 Tab2:** CAFÉ study participant timeline

	Pre-screening	Day 0	Day 7	Day 10	Day 90	Day 91	Day 150	Day 180	Day 365
EHR review eligibility	X								
Informed consent		X							
Randomization		X							
Baseline data collection		X							
**Outcome evaluation**									
Participant-reported outcomes									X
EHR outcomes					X				X
**Intervention activities**									
Enhanced usual care activities		X							
Navigation visit (Arm 2)				X					
Navigation visit (Arm 3)				X		X	X		
Participant-initiated navigation (Arm 2, Arm 3)				X	X	X	X		
Closure contact (Arm 2, Arm 3)								X	
Adverse events reporting		X	X	X	X	X	X	X	X

### Sample size {14}

The study will enroll 185 participants at each site (total *n*=370; approximately 123 per randomization group). Primary outcome measures for Objective 1, are assessed via survey at 12 months. Assuming 20% attrition, the analytic sample size for Aim 1 outcomes will be 296 patients (*n*=99 per group). With a type 1 error rate of 0.05 (two-sided), we will have 80% power to detect effect sizes of Cohen’s *d* = 0.40 for continuous outcomes. For the primary outcome of financial distress, this translates to a least detectable difference of 0.96 on the InCharge financial distress scale (10-point measure) for pairwise comparisons between randomization groups, assuming a standard deviation of 2.4 [41]. For the binary financial hardship measures (secondary outcomes), the least detectable difference depends on the proportion reporting financial hardship in the comparison group. We have 80% power to detect at 17.4% difference in financial hardship if the reported rate is 35% in the comparison group, corresponding to a rate of 17.6% among intervention patients (pairwise comparison of randomization groups). If the rate among comparison patients is much lower at 15%, the least detectable difference is 11.4%.

Based on our estimated sample size and a standard deviation of 5.0 as reported in the measure development work establishing the validity and reliability of the FACT-G7 in ambulatory cancer patient population [42], we estimate that we will be able to detect a 2.0-point difference in health-related quality of life (HR-QOL) between intervention and control groups. Since a 2 to 3 point difference on the FACT-G7 is considered clinically meaningful [42], we will be able to detect clinically meaningful changes on the FACT-G7 during the CAFÉ study.

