## Statistical methods

### Statistical methods for primary and secondary outcomes {20a}

#### Analysis of the primary endpoint(s)

The trial has two primary outcomes, financial distress, and cancer-specific health-related quality of life (HR-QOL). Both of these outcomes are continuous measures, which will be assessed via survey at 12 months after randomization. Financial distress will be measured using the InCharge Financial Distress/Financial Well-Being scale, and HR-QOL will be measured by the cancer-specific FACT-G7 scale.

Each outcome will be evaluated in a separate model. We will use linear regression models to estimate group means, using generalized estimating equations (GEE) with an independent working correlation structure and robust covariance estimation. The dependent variable will be the 12-month study outcome (financial distress, or HR-QOL), and the independent variables will be indicator variables for randomization group. Models will account for the clustering of patients within oncology departments. Estimates of intervention effects will be presented as differences in group means, with 95% confidence intervals. We will fit unadjusted models, and models adjusting for covariates, and models adjusting for measures imbalanced by randomization group, related to missing outcome data, and baseline measures of the outcome (where appropriate).

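### Two primary outcomes and two intervention arms give four primary tests against control, each sized at the full two-sided 0.05, so the stated 80% power holds per comparison only

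*Protocol article*

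**What the plan says.** Under Analysis of the primary endpoint(s), the protocol article names two primary outcomes at 12 months: financial distress (InCharge) and cancer-specific quality of life (FACT-G7). It states "Each outcome will be evaluated in a separate model", with indicator variables for the three randomization groups as the independent variables. The section on secondary endpoints combines the two navigation arms for the 3-month outcomes, as an exception to the general approach. The 12-month primary models therefore keep the arms apart.

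Sample size {14} says "With a type 1 error rate of 0.05 (two-sided), we will have 80% power to detect effect sizes" of d = 0.40, with 99 analysed patients per group. On the InCharge outcome it says: "this translates to a least detectable difference of 0.96 on the InCharge financial distress scale (10-point measure) for pairwise comparisons between randomization groups". The SD behind that figure is 2.4. For FACT-G7: "Based on our estimated sample size and a standard deviation of 5.0" (from the instrument's development work), "we estimate that we will be able to detect a 2.0-point difference" between intervention and control. Because 2 to 3 points is taken as clinically meaningful, the section concludes that "we will be able to detect clinically meaningful changes on the FACT-G7 during the CAFÉ study".

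Objectives {7} states the primary hypotheses for both outcomes without saying whether one or both must be met. It places the comparison of extended with brief navigation under Aim 3.

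**The concern.** Each of the two outcome models yields two contrasts against enhanced usual care, so there are four primary tests. The power statement spends 0.05 on every one of them. The article names no primary contrast, testing order, gate or division of alpha.

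Two things follow if the text is applied as written. First, a positive primary result could rest on any one of four tests, with an overall error rate well above 5%. Second, the detectable differences of 0.96 and 2.0 points describe a single comparison viewed alone. Any plan that divides alpha would contradict them, and a fixed testing order would preserve them for the first test only. The FACT-G7 statement has no slack on a pairwise reading, since 2.0 points is both the detectable difference and the lower end of the range called meaningful.

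**Working it through.** **Inputs.** From Sample size {14}: two-sided 0.05, 80% power, 99 per group, d = 0.40, SD 2.4 (InCharge) and 5.0 (FACT-G7). From Statistical methods {20a}: two primary outcomes, separate models, arm indicators. The correlation ρ between the two outcomes is not given. It is assumed here to lie between 0 and 0.7.

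**1. The plan's own figure.** The noncentrality is d√(n/2) = 0.40 × √49.5 = 2.81. With a two-sided 0.05 t-test on 196 df, power is 79.97%; the normal approximation gives 80.4%. The differences are 0.40 × 2.4 = 0.96 and 0.40 × 5.0 = 2.0. The stated figures reproduce, at 0.05 per comparison with 99 v 99.

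**2. Number of primary tests.** 2 outcomes × 2 navigation arms v control = 4.

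**3. Chance of at least one false positive when no arm has any effect.** Within an outcome, the contrasts are Z₂ = (M₂ − M₁)/√2 and Z₃ = (M₃ − M₁)/√2, where M is an arm mean in standard-error units. They share the control arm, so their correlation is 0.5. Simulation gives about 9.1% for one outcome. With two uncorrelated outcomes this is 1 − (1 − 0.091)² ≈ 17.3%. Simulation with correlated outcomes:

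| ρ (assumed) | Any false positive, either direction |
|---|---|
| 0 | 17.3% |
| 0.3 | 16.9% |
| 0.5 | 16.2% |
| 0.7 | 14.9% |

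Counting only errors in the direction of benefit gives about 9% (ρ = 0), 8% (0.5) and 7% (0.7).

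**4. Power with two-sided 0.025 per outcome (t-test).**

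- Pairwise, 99 v 99: the noncentrality is still 2.81, and power at d = 0.40 is 71%. For 80% power d must be 0.441, which is 0.441 × 2.4 = 1.06 InCharge points and 0.441 × 5.0 = 2.2 FACT-G7 points.
- Pooled navigation v control, 198 v 99: the noncentrality is 0.40/√(1/198 + 1/99) = 3.25, and power is 84%. For 80% power d must be 0.381, which is 0.91 InCharge points and 1.9 FACT-G7 points.

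**5. Does a gate followed by pairwise tests control the error?** Take the case where Arm 3 truly works on outcome 1 and nothing else has an effect. Outcome 1's gate passes almost surely, and Arm 2 v control is then a true null tested at 0.025.

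- If outcome 2 stays at 0.025, the overall error (outcomes independent) is about 1 − 0.975 × 0.975 = 4.9%.
- If passing outcome 1's gate also raises outcome 2 to 0.05, it is about 1 − 0.975 × 0.95 = 7.4%.

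Holding each outcome's family at 0.025 therefore keeps the total below 5%; releasing alpha on the gate alone does not.

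**The case against.** The strongest reply is that multiplicity rules commonly sit in an analysis plan, which is not shown, and that the sample-size arithmetic is right. Both statements are true, and the absence of a multiplicity procedure from the article is not the point made here. What stands is that the article already commits to a power figure that uses the full 0.05 for each pairwise test of two primary outcomes, without labelling it as per comparison.

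The second reply is that the error rate is conditional, and this is correct. It rests on an assumed correlation, on a rule that either outcome in either arm suffices, and on counting errors in both directions. The hypotheses are directional, and for false claims of benefit the figure is about half as large. If both outcomes had to succeed, it would be lower.

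The third reply is that the FACT-G7 sentence speaks of intervention against control, not of pairwise comparisons, and that the planned models adjusting for the baseline outcome could recover precision. The first part is fair. However, the 2.0-point figure is what 99 v 99 gives, and the 12-month models do not pool the arms. The gain from baseline adjustment depends on a correlation that the article does not give, so it cannot be credited here.

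**Conclusion.** The point holds in a bounded form. As written, there are four primary tests against control at 0.05 each. If any one may support a claim, the family-wise error is about 15–17% in either direction for ρ from 0 to 0.7, and about 7–9% for a false claim of benefit. The 80% power at d = 0.40 is valid per comparison only.

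A reader might infer more, and the document does not support it:

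- **Six primary tests, with an error above 20%.** This counts Arm 3 v Arm 2 as primary, but Objectives {7} puts that comparison under Aim 3.
- **16–17% as a floor.** The figure falls as the outcomes become more correlated: 14.9% at ρ = 0.7 and 12.6% at ρ = 0.9.
- **The trial cannot detect a meaningful FACT-G7 difference once error is controlled.** At 0.025 the pairwise figure is 2.2 points, inside the 2-to-3-point range the protocol cites, and the pooled figure is 1.9.
- **The sample size is miscalculated.** It is not; it reproduces exactly on its own terms.

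**What to change.** 1. State the success rule: benefit on either primary outcome, or on both. This is the sponsor's choice.
2. If either suffices, give each outcome's family two-sided 0.025. Within each outcome, test one gate first at 0.025: the 2-df test across arms, or pooled navigation v control. Go on to the pairwise contrasts at 0.025 only if the gate passes. Do not pass alpha to the other outcome on the gate alone.
3. If both must succeed, no split across outcomes is needed, but restate power for the joint rule. For one arm with d = 0.40 on both outcomes at 0.05, it lies between about 0.80 × 0.80 = 64% (uncorrelated outcomes) and 80% (perfectly correlated).
4. In Sample size {14}, label the present figures as per comparison. Under the either-outcome rule, add the restated ones: pairwise d = 0.44 (1.06 InCharge, 2.2 FACT-G7), with 71% power at d = 0.40; and, if the pooled gate is chosen, d = 0.38 (0.91 and 1.9), with 84% power.
5. Fix the rule before the partial unblinding that the article allows for the 3-month analysis, or confirm that an existing analysis plan already states it.

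The cost is a few sentences and a slightly less favourable pairwise detectable difference. A pooled gate would also add a contrast that the 12-month analysis does not now contain. No extra patients are needed.

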### Recruitment {15}

We will identify eligible participants using the CAFÉ study eligibility program (SEP). We have developed the SEP specifically to identify patients eligible for the CAFÉ study using electronic health record (EHR) data. Patients are eligible if they have a new cancer diagnosis and an initial visit to a participating CAFÉ study clinic following their diagnosis [43] in addition to meeting the other inclusion criteria. We have validated the SEP against manual chart review as the gold standard.

#### Equity-informed sampling

We established a goal that individuals from historically under-represented and under-studied populations will comprise up to 50% of the enrolled participants. We did this to maximize opportunities to identify unique insights from a more diverse study population, as well as to be responsive to the ethical principle of justice by promoting greater fairness in access to equal opportunity for participation and the distribution of the benefits and risks of the research.

Using EHR data, we will use the following four enrichment characteristics to identify individuals from populations historically under-represented and under-studied in clinical trials: non-White race; Hispanic ethnicity; Spanish as a preferred spoken language (KPNW only); and Medicaid beneficiary status. We will prioritize for recruitment of individuals who meet any of the four enrichment characteristics.

#### Manual chart review

Our initial SEP design and validation identified some areas where manual review is necessary to confirm an individual’s eligibility. Thus we include selective manual verification step to confirm participant eligibility for individuals whose CAFÉ-qualifying cancer diagnosis meets the following criteria: cancer type is the “Other” CAFÉ study cancer group (i.e., not breast, colorectal, lung, or prostate cancer); diagnosis is suggestive of a metastatic cancer diagnosis; or noted prior cancer diagnosis within 10 years different than the CAFÉ-qualifying cancer diagnosis (i.e., a new primary tumor that is diagnosed within 10 years of a prior primary tumor at a different site).

#### Recruitment procedures

To recruit participants, we will mail advance letters and a study information sheet. The information sheet will describe the study, include instructions on how to opt out, and state that we will call to invite them to participate in the study, obtain consent, and conduct the baseline survey.

## Assignment of interventions: allocation

### Sequence generation {16a}

After completion of baseline questionnaire, participants will be randomized via a computer-generated randomization scheme developed by a study biostatistician in a 1:1:1 ratio to study groups (Enhanced usual care, Brief intervention, or Extended intervention) stratified by site (KPWA; KPNW), and cancer type (breast, lung, prostate, colorectal, other). Our recruitment goal is to enroll a sample that reflects the distribution of cancer types in the underlying clinical population, and to enroll an equal number of participants at each study site. As such, we will flex the sampling during the recruitment period to meet this goal.

We will employ random blocks of sizes 3 and 6 to ensure balance of groups over time as well as blinding of study team to next randomization assignment. The biostatistician will keep the randomization file in a secure folder only accessible to the biostatisticians and programmer.

### Concealment mechanism {16b}

The study biostatistician will provide the study programmer with the randomization scheme within specified strata. The programmer will develop a program that will only allow participants to be randomized once they consent and complete the baseline questionnaire. This method ensures that treatment allocation cannot be changed after randomization.

### Implementation {16c}

The study biostatistician will generate the allocation sequence. Study staff will enroll participants. After consenting and collecting baseline data from the participant, the study interviewer will press a button within the REDCap database and the appropriate group assignment will be revealed.

## Assignment of interventions: blinding

### Who will be blinded {17a}

This is an unmasked trial for participants and study interventionists, as it is not possible to provide the intervention without revealing the study group.

The survey administrators will be blinded to study group assignment 12-month survey, where primary and secondary self-reported outcomes will be collected. Baseline data collection will be conducted before randomization.

No members of the core study team, including PI’s, biostatisticians, programmers, or interventionists will have access to unblinded data. Study biostatisticians and programmers may access data (blinded by study arm) for quality control and study progress reporting purposes, as necessary.

### Procedure for unblinding if needed {17b}

Partial unblinding (study group assignment to “any intervention” vs. “enhanced usual care”) will occur to biostatisticians and programmers only at the time of analysis of 3-month EHR outcomes. Otherwise, unblinding will only occur once the final 12-month outcomes dataset is assembled and locked.

## Data collection and management

### Plans for assessment and collection of outcomes {18a}

All recruitment and participant-reported outcomes data is collected and stored in a bespoke REDCap study database developed by the study team.

#### Survey

Participant-reported outcomes and covariate data will be collected via telephone survey at baseline and 12 months. Trained survey administrators will conduct all surveys using IRB-approved survey instruments. Survey administrators will enter survey data directly into the study REDCap database.

#### Administrative data

EHR-based data will be collected at baseline, 3 months, and 12 months, including covariate and outcome data. Data to be collected will be consistent across study sites. Data sources include virtual data warehouse (VDW) data elements developed by the Healthcare Systems Research Network (HCSRN) and EPIC® Clarity.

#### CAFÉ navigator notes and closure questions

CAFÉ navigators will use the study REDCap database to conduct all intervention activities. Navigators are trained in the use and administration of the database for both intervention administration and entering of research data that will allow assessment of participant dose received and intervention fidelity and adherence. Fields in the database are both open text (e.g., to describe resources provided to a participant) and discrete fields (e.g., completion of an assessment visit; type of financial concern addressed in visit).

Navigators will, at each intervention participant’s closure call, ask four brief questions about the participant’s experience with the intervention and make field notes summarizing the participant’s answers to these questions in an open text field.

Copies of surveys and data dictionaries are available on request to the principal investigators.

### Plans to promote participant retention and complete follow-up {18b}

Study staff collecting survey outcomes will attempt to reach participants up to 5 times for baseline and follow-up data collection. Participants will receive an incentive of $10 for completion of the baseline survey $25 for completion of the follow-up survey.

